### Data collection

Data will be obtained by history from the participant or extracted from the clinical notes. These include:

1. Participant information - age, gender, weight, height, allergies, cause of kidney disease, co-morbidities

2. Date of PD catheter insertion and start of this period of peritoneal dialysis

3. Type of PD catheter and the technique by which PD catheter was inserted

4. Previous dialysis history

5. PD related complications

6. HD related events

7. Laboratory investigations - full blood count, electrolytes, coagulation profile, liver function test and C-reactive protein at admission to hospital as part of usual care.

8. Microbiology results - Gram stain, culture and antimicrobial sensitivities of dialysate fluid at admission to hospital if there is clinical suspicion of peritonitis

9. Antibiotics and other drugs prescribed concomitantly

10. Length of stay in hospital.

### Statistical considerations

The proposed sample size is 315 patients, 105 per group. A prospective study conducted in a single centre (RBWH) showed a complication rate of 38% with immediate use and 2.56% with a two week delay period [9]. Unpublished data of complication rates with four weeks delay period were quoted as 1-2 in 30 cases. To obtain 80% power with an overall 1-sided significance level of 0.05, approximately 105 patients are required per group to establish non-inferiority, defined as a difference in complication rates less than 10% between two groups. It was assumed that the expected complication rate was 3% as estimated from the preliminary data, and the significance level was adjusted for multiple comparisons. Sample size calculations were performed using ACCorD (Analysis of Censored and Correlated Data, Version 1.6.9, 2010).

### Data analysis

The outcome variables, both primary and secondary, are binary. Hence the outcomes will be analysed using logistic regression to compare the three arms of time to dialysis, adjusting for diabetes or not. Outcomes will be analysed using the statistical program SPSS.

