## Discussion

This study targets patients with end stage kidney disease who choose PD for maintenance therapy. Current practice at some centres and at the RBWH [10] is to wait four weeks after a Tenckhoff catheter is placed before starting PD. A few centres start PD immediately after insertion [16] or after a week. Several Australian centres wait for two weeks and the CARI guidelines suggest a two-week delay. There is no consensus in the literature on optimal time interval between peritoneal catheter insertion and start up of dialysis. This is a randomised study to compare the complication rates in one, two, and four weeks delay in initiating PD from the time of insertion of PD catheter. Safety will be measured by assessing adverse events as a consequence of starting PD. The hypothesis is that there is no difference in complication rate between one, two and four weeks delay. If non-inferiority is demonstrated between one, two and four weeks delay in this trial then we could justifiably decrease the duration of delay significantly. The benefit to future patients would be fewer HD episodes, shorter duration of HD catheter placement, fewer HD catheter infections and fewer HD catheter replacement requirements. Results showing more complications in the one or two week delay groups will influence the current international guidelines, based on an appropriate risk/benefit analysis.

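### The trial is sized for non-inferiority on a 10-point risk difference, but the stated logistic comparison of arms and the no-difference hypothesis do not test it

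*Protocol article*

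**What the plan says.** Three places in the protocol article bear on this.

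- **Statistical considerations** fixes the design: "The proposed sample size is 315 patients, 105 per group". The aim of that number is "to establish non-inferiority, defined as a difference in complication rates less than 10% between two groups", with 80% power and an overall one-sided level of 0.05. The planning assumption is that "the expected complication rate was 3% as estimated from the preliminary data, and the significance level was adjusted for multiple comparisons". The adjusted level and the number of comparisons are not given.
- **Data analysis** notes that the outcomes are binary and continues: "Hence the outcomes will be analysed using logistic regression to compare the three arms of time to dialysis", with diabetes as the covariate. It mentions no margin, risk difference, one-sided limit or adjusted level.
- **Discussion** states the hypothesis: "The hypothesis is that there is no difference in complication rate between one, two and four weeks delay". The sentence after it says that a shorter delay could be justified if non-inferiority is shown.

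**The concern.** The sample size, the hypothesis and the analysis answer different questions. The sample size asks whether an earlier start is worse by less than 10 percentage points. The hypothesis and the logistic comparison ask whether the arms differ at all, and express the answer as odds ratios. Failing to find a difference is not evidence that any difference is small, least of all when few events are expected.

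This is the primary outcome, and the article ties its result to shortening the delay in practice. An analyst who followed the Data analysis section to the letter would produce odds ratios and p-values, and would have no rule for turning them into the non-inferiority conclusion that the trial was sized to reach.

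**Working it through.** **Inputs.** From Statistical considerations: 105 per group, assumed rate 3% in every arm, margin 10 points, overall one-sided 0.05, 80% power. From Data analysis: logistic regression on the three arms. My assumptions: no dropout, and illustrative levels of 0.05, 0.025 (two comparisons) and 0.05/3 (three comparisons), because the adjusted level is not given.

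**The plan's own figure.** With unpooled variance, n = (z_α + z_β)² × [2 × 0.03 × 0.97] / 0.10².
- α = 0.05: (1.645 + 0.842)² × 5.82 gives 36 per group.
- α = 0.025: 46 per group.
- α = 0.05/3: 52 per group.

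The Farrington-Manning score formula gives 60, 78 and 88. It comes to 106, next to the stated 105, only under choices that the article does not state: α = 0.05/6, or α = 0.025 with about 93% power per comparison (0.80^(1/3) = 0.928, joint power over three comparisons). The figure of 105 is therefore neither confirmed nor shown wrong. The point does not depend on it.

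**Error if non-significance is taken as support.** Let the earlier-start arm be exactly at the margin, 13% versus 3%, so that a claim of non-inferiority would be false. On the odds scale this is (0.13/0.87)/(0.03/0.97) = 4.83. With 105 per arm:

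| Rule | Trials giving false support |
|---|---|
| Pairwise logistic Wald test non-significant, two-sided 0.05 | about 27% |
| Pairwise logistic Wald test non-significant, one-sided 0.05 | about 17% |
| 2-df likelihood-ratio test non-significant (13%/3%/3%) | about 14% |
| Score non-inferiority test, one-sided 0.05 | 4.4% |
| Score non-inferiority test, one-sided 0.05/3 | 1.3% |

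The pairwise rows are by exact binomial enumeration and the 2-df row is by simulation. The logistic rows omit the diabetes term.

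**Power of the matching test.** At 3% versus 3%, the score test passes in about 98% of trials at one-sided 0.05 and 90% at 0.05/3. The Farrington-Manning approximation gives 97%, 93% (at 0.025) and 89%. If the margin were instead moved to the odds scale (4.83) and tested with a Wald limit, power would fall to about 56% at 0.05 and 41% at 0.05/3.

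**Two examples with 105 per arm.**
- *10 versus 3 events.* OR = (10/95)/(3/102) = 3.58. The SE of log OR = √(1/10 + 1/95 + 1/3 + 1/102) = 0.674, so z = 1.275/0.674 = 1.89 and p = 0.058: no significant difference. The risk difference is 7/105 = 6.7 points with a one-sided 95% upper limit (Newcombe) of 12.7 points: the margin is not met.
- *3 versus 3 events.* OR 1.00, 95% CI 0.20 to 5.07, which looks uninformative. The upper limit of the risk difference is 4.4 points: clearly inside the margin.

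The mismatch can mislead in both directions.

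**Sparseness.** Expected events are 315 × 0.03 = 9.45. At the upper end of the four-week data ("Unpublished data of complication rates with four weeks delay period were quoted as 1-2 in 30 cases") they would be 315 × 2/30 = 21. At 3%, P(no events in a given arm) = 0.97^105 = 4.1%, and P(at least one empty arm) = 1 − (1 − 0.0408)³ = 11.8%. Ordinary maximum likelihood cannot estimate an odds ratio for an empty arm.

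**The case against.** Several objections have force.

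- *Logistic regression can serve non-inferiority.* This stands. Fitted risks from the model give a risk difference and a one-sided limit. With an arm-only model and a delta-method limit, such a test passes in 99% (0.05) and 97% (0.05/3) of trials at 3% versus 3%. At the margin it wrongly passes in 6.4% and 2.7%: slightly too often, but usable. A reader might infer that the chosen model is incapable of the task. It is not; what is missing is the margin-based comparison.
- *The article never says that non-significance will count as non-inferiority.* This also stands. The Discussion makes its conclusion conditional on non-inferiority being demonstrated. The 14% to 27% describe what happens if the stated test is used for that conclusion, not a rule that the authors have adopted.
- *The definition of non-inferiority could be read as a rule on the observed difference.* That reading is strained. The same sentence gives power and a significance level, which an observed-difference rule would not have; the wording is ordinary shorthand for a margin.
- *A moderate true excess might also go undetected.* A true 10% versus 3% is a 7-point difference, inside the margin. A favourable conclusion there would not be an error under the plan's own definition, so it is no evidence of harm.
- *Interval method, multiplicity procedure and empty-arm handling belong in a full protocol or SAP.* Agreed, and their absence is not the point. The point is that the analysis and hypothesis that the article does state do not match the objective on which it is sized.

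**Conclusion.** The point holds as a mismatch between stated items. The design is non-inferiority on an absolute difference; the stated hypothesis and analysis are a comparison for difference on the odds scale. Used to support a shorter delay, a non-significant result would be wrong at the margin in about 14% to 27% of trials, depending on the test and its sidedness, against a planned 5% at most.

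These figures assume 105 evaluable patients per arm and a 3% reference rate. The sample size is not the problem: at 3% it supports a proper margin test with about 90% pairwise power even at 0.05/3. That reassurance weakens if the rate is nearer 2 in 30. The unpooled formula, the more favourable of the two used here, then needs (2.128 + 0.842)² × 2 × 0.0667 × 0.9333 / 0.01 ≈ 110 per group at 0.05/3.

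**What to change.** - **Hypotheses.** For each comparison, state H0 as a risk difference (earlier start minus later start) of 10 points or more, and the alternative as less than 10 points. Replace the no-difference hypothesis in the Discussion.
- **Primary analysis.** Estimate the risk difference for one versus four weeks and for two versus four weeks. Four weeks is a natural reference because the Discussion gives it as current practice at the Brisbane site; the article names no reference arm, so this must be stated. Use a score (Miettinen-Nurminen type) interval or a difference standardised from the logistic model, accounting for the stratification factors, site and diabetic status.
- **Decision rule.** Declare non-inferiority only if the one-sided upper limit is below 10 points, at an explicitly stated adjusted level. Examples are 0.025 for two comparisons or 0.05/3 for three. The level and number of comparisons must match the sample-size calculation, which says "the significance level was adjusted for multiple comparisons" without giving them.
- **Supportive analysis.** Keep the odds ratios. With about 9 events expected at 3%, name a penalised (Firth) fit as the fallback if an arm has no events.

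The cost is a rewritten analysis paragraph, one changed sentence in the Discussion and a few lines of code. No new patients or data are needed. The sponsor must retrieve the adjusted level from the original sample-size run.

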## Background

Peritoneal dialysis (PD) catheters are inserted surgically or laparoscopically into the peritoneal cavity for the initiation of PD. The best time to use a PD catheter after its insertion is not clear from the literature. Complications such as dialysate fluid leaks and infection at the exit site or peritonitis can occur if PD is initiated too soon after insertion of the catheter [1]. Bridging hemodialysis (HD) may be required if PD is delayed [2]. Morbidity and expense could be saved by earlier initiation of PD post Tenckhoff catheter insertion that would limit the requirement for bridging HD. Current practice varies widely. Studies reported in this area have been observational and mostly compare immediate with delayed use[3,4]. Some studies support delayed use but do not test different delay intervals and can not tell us the optimal time to initiate PD [5-7]. Recent studies report a very low leak incidence after short break in period, attributed to tight catheter securing [8,9]. However, there is a lack of control groups in all these studies. A single centre retrospective and subsequent prospective audit found less complications when dialysis was initiated two weeks after Tenckhoff catheter insertion compared with immediate use [10].

Delay in starting PD results in the need for bridging HD in patients who require immediate dailysis. Bridging HD usually requires temporary HD catheters, with attendant risk of complications [11] and is also more expensive than PD [12].

Guideline bodies, such as Caring for Australasians with Renal Impairemnt (CARI) recommend, based on Level III and IV evidence, starting PD two weeks post Tenckhoff catheter insertion and advocate randomised controlled trials and further research [13]. International guidelines (European Dialysis and Transplant Association-European Renal Association and International Society for Peritoneal Dialysis, 1998 [14]) also suggest a two week delay and state that there is insufficient evidence to formulate a "guideline".

Comparing lag periods of one, two and four weeks after insertion of Tenckhoff catheters will enable us to determine how much effect the duration of the delay has, if any, on PD complications while determining any advantage that earlier start may have in terms of limiting HD during the bridging period.

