### Identification of eligible patients

Patients who satisfy the inclusion and exclusion criteria will be recruited from pre-dialysis clinics, PD clinics, catheter insertion preadmission clinics, catheter insertion operating lists and the HD population. Written informed consent will be obtained from all participants.

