#### Secondary

Composite of all PD catheter related complications and HD requirements and associated complications. PD catheter related complications include fluid leaks, infection, cuff erosion, cuff extrusion, failure to establish PD successfully (may be due to blockage, fibrin plug or outflow obstruction), delayed wound healing, haematoma, catheter revision or replacement, conversion to HD, HD related events, allergic reactions, hospitalisation for any reason with cause recorded as related to either surgery or start up of dialysis and death during the study period.

Outcomes will be recorded for eight weeks following the insertion of the Tenckhoff catheter. However, primary outcomes will relate only to those events occurring within four weeks after start up of dialysis as these will best inform the question of optimal delay time.

The HD related events include the number of HD treatments required during the study period, the use of temporary HD vascular access (non-tunnelled and tunnelled central venous catheters) and a composite of HD vascular access complications - infection (exit site or bacteraemia or septicaemia), blockage requiring intervention eg urokinase, replacement, repositioning and/or removal

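### The haemodialysis-requirement outcomes are adjusted for diabetes only; adding dialysis status at catheter insertion would be a cheap, optional gain in precision

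*Protocol article*

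**What the plan says.** The Data analysis section of the protocol article states "The outcome variables, both primary and secondary, are binary" and continues: "Hence the outcomes will be analysed using logistic regression to compare the three arms of time to dialysis, adjusting for diabetes or not". It names no other covariate, and it does not separate the HD outcomes from the leak and infection outcomes.

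Four other places bear on this:

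- **Identification of eligible patients.** Recruitment runs from pre-dialysis clinics through to "catheter insertion preadmission clinics, catheter insertion operating lists and the HD population", so the sample mixes patients on HD with patients not yet on dialysis.
- **Background.** "Delay in starting PD results in the need for bridging HD in patients who require immediate dailysis". The same section makes limiting HD one of the questions of the trial.
- **Outcome measures, Secondary.** "The HD related events include the number of HD treatments required during the study period, the use of temporary HD vascular access", followed by a composite of access complications.
- **Data collection, item 4.** "Previous dialysis history" is recorded.

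Randomisation is stratified by site and diabetic status (Participants), not by dialysis status.

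**The concern.** A patient already on HD at insertion can be expected to go on having it until PD starts, and the shortest wait in any arm is one week. A pre-dialysis patient may need none. Dialysis status at insertion is therefore likely to predict HD use strongly, and the article offers no similar argument for diabetes. Neither the randomisation nor the named model deals with chance differences between arms in the share of patients on HD.

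The Discussion describes the benefit of a shorter delay in HD terms: fewer HD episodes and less HD catheter use, infection and replacement. If non-inferiority on leaks and infection is shown, the case for starting earlier rests on the HD comparison. Avoidable imprecision there matters, although the primary result is untouched.

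**Working it through.** **What the plan gives.** It states no power, rate or precision for any HD outcome. Its only sample-size figure, 105 per group, concerns the primary non-inferiority comparison. A Farrington-Manning calculation with 3% in both arms, a 10-point margin and 80% power gives 105.9 per group at one-sided 0.05/6 (power 79.5% at 105). That figure is used below only as the arm size.

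**Assumed inputs (none is in the article).** One-week versus four-week arm, two-sided 0.05, and a share *f* of patients on HD at insertion. In the base case every on-HD patient has some HD, and bridging HD in the rest is 10% versus 30%.

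**1. Yes/no HD, *f* = 0.3.**

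- Unadjusted rates: 0.3 + 0.7 × 0.10 = 0.37 and 0.3 + 0.7 × 0.30 = 0.51. The difference is 0.14.
- Null SE: √(2 × 0.44 × 0.56 / 105) = 0.0685. Alternative SE: √((0.37 × 0.63 + 0.51 × 0.49) / 105) = 0.0678.
- Power: Φ((0.14 − 1.96 × 0.0685) / 0.0678) = Φ(0.08) = 53%.
- Stratified: the on-HD stratum contributes a zero difference with no variance. In the rest there are 0.7 × 105 = 73.5 per arm and the difference is 0.20. Null SE: √(2 × 0.2 × 0.8 / 73.5) = 0.0660. Alternative SE: √((0.09 + 0.21) / 73.5) = 0.0639.
- Power: Φ((0.20 − 1.96 × 0.0660) / 0.0639) = Φ(1.11) = 87%.

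The Mantel-Haenszel risk difference is 0.3 × 0 + 0.7 × 0.20 = 0.14, the same quantity as the unadjusted difference. Its SE is 0.7 × 0.0639 = 0.0447 against 0.0678.

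**2. Other shares, by the same formulas and by simulation** (pooled two-proportion test versus Cochran-Mantel-Haenszel test).

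| On HD at insertion | Formula, unadjusted vs stratified | Simulation, unadjusted vs stratified |
|---|---|---|
| 10% | 83% vs 94% | 84% vs 94% |
| 20% | 68% vs 91% | 69% vs 92% |
| 30% | 53% vs 87% | 52% vs 88% |
| 50% | 31% vs 73% | 32% vs 74% |

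**3. Weaker assumptions (simulation).**

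- On-HD patients positive in 80% vs 95%, others 20% vs 40%, *f* = 0.3: about 75% vs 89%.
- On-HD patients positive in 70% vs 95%, others 10% vs 30%, *f* = 0.3: about 90% vs 98%.
- All on-HD patients positive, others 30% vs 50%: 62% vs 76% at *f* = 0.2, and 35% vs 55% at *f* = 0.5.
- Logistic regression with and without the covariate, over a wider grid: the ratio of squared z statistics (unadjusted to adjusted) ran from 0.27 to 0.93, a loss of 7% to 73%. At *f* = 0.3 with four-week rates of 0.5 (on HD) and 0.2 (not on HD) and a log odds ratio of −0.9, power was 70% vs 74%. With 0.9 and 0.2 it was 41% vs 64%.

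**4. Number of HD treatments.** Assume three sessions a week while waiting if on HD. Assume bridging in 10% vs 30% of the rest, starting at a uniform time in the wait. At *f* = 0.3:

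- On HD: 12 − 3 = 9 sessions. Not on HD: 0.30 × 6 − 0.10 × 1.5 = 1.65 sessions.
- Difference: 0.3 × 9 + 0.7 × 1.65 = 3.9 sessions. The unadjusted SE is about 0.55, so z is about 3.9 / 0.55 = 7.
- Unadjusted power was about 100% for shares from 5% to 70%.
- In simulations of session counts at about three a week, the variance ratio (unadjusted to stratified) was about 1.5 to 2.1. The interval narrows by 1 − 1/√1.5 = 18% to 1 − 1/√2.1 = 31%.

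**The case against.** The strongest reply is that nothing here is wrong. Randomisation keeps the unadjusted comparison valid, diabetes is a stratification factor and so a standard covariate, and a condensed article may leave further covariates for secondary outcomes to the full plan. The text does not bar them. This stands as far as severity goes. It does not remove the point, because the article is not silent: it names one covariate for every outcome, and that choice suits the HD outcomes poorly.

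Other replies, and what remains of them:

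- **Any HD, yes/no, is not listed as a separate outcome; the number of treatments is.** True. But the article calls all secondary outcomes binary, so HD requirement as analysed implies a dichotomy. The conflict between a count and that statement is a separate matter.
- **The large gaps depend on every on-HD patient having HD.** Correct. Relaxing this shrinks the gap, though stratification gained power in every case run.
- **Status at insertion is not a listed data item.** Correct. It must be derived from dialysis history.
- **Patients not on HD may also need bridging.** Entry is for patients meant to use the catheter as soon as possible, which weakens the covariate. This supports giving a range.
- **Adjusted and unadjusted odds ratios are different estimands.** Correct. A stratified risk difference avoids the problem.

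A reader might infer that the trial discards about half of its information on HD, or that a real saving in HD would probably be reported as no difference. The article supports neither. The first needs an on-HD share and HD rates that it does not give. The second fails for the session count, where unadjusted power is about 100% under the inputs above.

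**Conclusion.** The point holds as an optional precision improvement on secondary outcomes. It is not an error and it does not bias any result. The direction is firm: the article itself links need for dialysis to bridging HD, mixes patients by dialysis status, and collects the history, yet adjusts for diabetes alone.

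The size is uncertain. For yes/no HD it runs from a gap of a few points of power, when status predicts weakly, to 32% versus 74% when half the patients are on HD and all of them have HD while waiting. For the number of treatments the gain is a narrower interval, not a rescued comparison. All of this rests on assumed shares and rates, 105 per arm, and a one- versus four-week contrast at two-sided 0.05.

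**What to change.** In Data analysis, add one sentence: the HD-requirement outcomes will be compared adjusting for, or stratified by, dialysis status at catheter insertion (on HD or not, derived from the dialysis history item) in addition to diabetes.

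- For yes/no HD, if nearly all on-HD patients are positive, use a stratified Mantel-Haenszel estimate, preferably a risk difference. The effect then stays marginal, and a stratum near 100% does not destabilise a logistic model.
- Leave the primary leak and infection model as it is. At an expected rate of 3% it has few events (about 0.03 × 105 = 3 per arm) and should not carry more terms.

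The cost is one extra baseline term in the secondary HD models, and a check that the history item records status at insertion. It adds no patients, visits or procedures. Prespecifying the term also avoids choosing a covariate after the data are seen.

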**Methods/Design:**

This is a randomised controlled trial of patients who will start PD after insertion of Tenckhoff catheter at Royal Brisbane and Women's Hospital (RBWH) or Rockhampton Base Hospital (RBH) who meet the inclusion criteria. Patients will be stratified by site and diabetic status. The patients will be randomised to one of three treatment groups. Group 1 will start PD one week after Tenckhoff catheter insertion, group 2 at two weeks and group 3 at four weeks. Nurses and physicians will be blinded to the randomised allocation. The primary end point is the complication rate (leaks and infection) after initiation of PD.

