### Setting

The Department of Renal Medicine, RBWH and RBH service populations of approximately 1.2 million and 200,000 respectively. This study is conducted by the 'Home Independent dialysis and Transition Program' (HITS) of the Department of Renal Medicine, RBWH and the Peritoneal Dialysis Service of RBH.

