### Participants

Participants will be stratified by site and diabetic status. The patients will then be block randomised in equal proportions to the three treatment groups using randomly varying blocks of size three and six. The randomisation sequence was generated using Stata 11 software [15]. Group 1 will start dialysis one week after Tenckhoff catheter insertion, group 2 at two weeks and group 3 at four weeks. A research nurse independent of study nurses and physicians will undertake randomisation process.

Patients will initiate dialysis in equivalent fashion apart from the study variable of delay period before initiation. The patients will be trained by the PD nurses in their respective centres. The PD exit site and tunnel will be examined according to the usual clinical practice at each site to detect any complications. This will not interfere with routine dressing changes or reviews currently in practice.

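### Randomisation is stratified by site and diabetic status, but the stated model adjusts for diabetes only; the effect is small and conservative

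*Protocol article*

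**What the plan says.** Two places in the protocol article describe the stratification, and they agree. The abstract (Methods/Design) has "Patients will be stratified by site and diabetic status", and the Participants section has "Participants will be stratified by site and diabetic status". Within strata, patients are "block randomised in equal proportions to the three treatment groups using randomly varying blocks of size three and six".

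The Data analysis section states that "the outcomes will be analysed using logistic regression to compare the three arms of time to dialysis", and adds "adjusting for diabetes or not". Site is not mentioned there as a covariate, a stratum or a random effect, and no other section brings it in.

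Three further statements bear on the size of the problem:
- The two hospitals "service populations of approximately 1.2 million and 200,000 respectively" (Setting).
- The exit site and tunnel are "examined according to the usual clinical practice at each site to detect any complications" (Participants).
- "The proposed sample size is 315 patients, 105 per group" (Statistical considerations), planned on a 3% complication rate and a 10-point non-inferiority margin.

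**The concern.** An analysis should normally carry the factors that restricted the randomisation. Blocking within site balances the arms on site, so differences between sites cannot add noise to the arm comparison. A model that omits site still counts those differences as error, and its standard errors do not reflect the design.

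This is more than a detail left to a fuller document. The article names its adjustment set, includes one of its two stratification factors and omits the other. A later analyst could reasonably take site to have been left out on purpose.

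There is some ground for thinking that event rates may differ by hospital. Leaks, exit-site infection and tunnel infection are part of the primary outcome, and the examination that finds them follows local practice. Training is also given locally. What is at stake is a little precision in a non-inferiority trial with few events, and agreement between design and analysis.

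**Working it through.** **Text comparison.** Factors used at randomisation: site and diabetic status. Factors named in the model: diabetes. Omitted: site. The adjustment phrase most naturally means diabetic status, yes or no. If it is read as with or without adjustment for diabetes, site is still absent.

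The plan has no figure on this point to reproduce. The calculations below only gauge how much the omission could matter.

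**Inputs from the article.** 105 patients per arm; 3% expected rate; 10-point margin; overall one-sided level 0.05, adjusted for multiple comparisons by an unstated method; catchments of 1.2 million and 0.2 million.

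**Assumptions.**
- The smaller hospital enrols 0.2/1.4 = 1/7 of patients, about 15 per arm and 315/7 = 45 in all.
- The level per comparison is 0.05/3 = 1.67%.
- The larger and smaller hospitals have rates of 3% and 3%, 2.5% and 6%, or 2% and 9%. Each pair averages 3%: for example, (6/7)(2%) + (1/7)(9%) = 3%.

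**Expected effect on the standard error.** For a risk difference with no true arm effect, ignoring site uses the variance p(1 − p) = 0.03 × 0.97 = 0.0291 per patient. The design leaves only the within-site part, which is smaller by (6/7)(1/7)(difference in site rates)².

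| Site rates | Between-site part | Within-site variance | SE ratio, ignoring site / by site |
|---|---|---|---|
| 3%, 3% | 0 | 0.02910 | 1.000 |
| 2.5%, 6% | (6/49)(0.035²) = 0.00015 | 0.02895 | √(0.02910/0.02895) = 1.003 |
| 2%, 9% | (6/49)(0.07²) = 0.00060 | 0.02850 | √(0.02910/0.02850) = 1.010 |

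**Simulation.** The setting was two arms of 105, 20,000 replicates, and a Wald test of the 10-point margin, with and without stratifying by site. Diabetes was not modelled.

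| Site rates | Mean SE, ignoring / by site | Power, ignoring / by site | Rejection when truly 10 points worse, ignoring / by site |
|---|---|---|---|
| 3%, 3% | 0.02296 / 0.02285 (+0.5%) | 96.9% / 97.0% | 2.7% / 2.8% |
| 2.5%, 6% | 0.02291 / 0.02265 (+1.1%) | 97.0% / 97.3% | 2.7% / 2.9% |
| 2%, 9% | 0.02298 / 0.02247 (+2.3%) | 97.2% / 97.6% | 3.0% / 3.3% |

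The 0.5% at equal rates is not a site effect. The plug-in variance is biased low by a factor of 1 − 1/105 when pooled and, on average, 1 − 2/105 when split over two sites. The ratio √[(1 − 1/105)/(1 − 2/105)] = 1.005 accounts for it. The simulated 0.5% to 2.3% is thus, if anything, a generous estimate of the loss.

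The rejection rates exceed 1.67% under both analyses because the Wald approximation is poor with few events. Ignoring site does not raise them.

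**Effect on the odds ratio.** Take a within-site odds ratio of 2. With reference rates of 2.5% and 6%, the comparison-arm rates are 4.88% and 11.32%, which average 5.80%. The pooled odds ratio is (0.0580/0.9420)/(0.03/0.97) = 1.99. With 2% and 9%, the comparison-arm average is 5.72% and the pooled odds ratio is 1.96. The shifts in log odds ratio are ln(2/1.990) = 0.005 and ln(2/1.962) = 0.019. The standard error is about 0.71, from √(1/3.15 + 1/101.85 + 1/6.1 + 1/98.9).

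**Sparse data.** Expected events are 315 × 0.03 = 9.45. At 3%, the chance of no event among 45 patients at the smaller hospital is 0.97^45 = 25%.

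**The case against.** The best case for leaving the plan alone is that the effect is negligible and the omission may be sensible. Two arm terms and diabetes already strain a model with 9 to 10 events. If the smaller hospital has none, an ordinary maximum-likelihood site coefficient has no finite estimate. The article also applies common outcome definitions at both hospitals (Table 1) and has dialysis start in the same way apart from the delay, which weakens the case that site is prognostic. Nor does it say in so many words that diabetes is the only covariate.

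Most of this stands as to size. It does not remove the mismatch: one stratification factor is named in the model, the other is not, and sparsity is not offered as a reason. Sparsity bears on how to include site, since stratum weighting and penalisation both cope with it.

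A reader might infer two stronger things, and neither is supported.
- **An invalid test, or false non-inferiority made easier.** Standard errors err on the large side, and the rejection rates show no inflation from ignoring site.
- **An odds ratio biased towards no difference.** The shift is non-collapsibility: pooled and within-site odds ratios are different quantities. At most 0.019 against a standard error of 0.71, it could not change a reading.

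It would also go too far to say that site is known to matter. The article reports no rates by site, and its figure for a two-week delay comes from one hospital.

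**Conclusion.** The point holds as a mismatch between design and analysis with a minor, conservative consequence. That site is stratified on and then missing from the stated model follows from the text alone. The size rests on the assumed one-seventh share, the assumed site rates and a risk-difference test. On that basis the cost is nil if rates are equal. At 2% against 9%, it is about 2% in the standard error and 0.4 points of power. The article's stated method is logistic regression, so these figures indicate scale and do not predict the trial's own analysis. The planned sample size is unaffected.

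**What to change.** Include both stratification factors in the primary analysis, in one of two ways:
- **Preferred:** a Mantel-Haenszel type risk difference stratified by site and diabetes (four strata). This is on the scale of the 10-point margin. A score-type interval such as Miettinen-Nurminen is better than a Wald interval here.
- **Alternative:** a Firth-penalised logistic model with main effects for site and diabetes. Its odds ratios would have to be converted to a risk difference to be read against the margin.

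With about 9 to 10 events expected, use no interaction terms and do not rely on ordinary maximum likelihood. If site is to stay out, give the reason before outcome data are seen.

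The change needs a sentence or two in Data analysis and no new data. Its small downside is a sparse-data method in place of standard logistic regression.
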